### Recruitment {15}

In our department, several new residents are beginning their first residency. We previously conducted a study on resident starters in our department, and we have calculated a study period of approximately 3 years to examine the 30 career starters [1].

## Assignment of interventions: allocation

### Sequence generation {16a}

At the beginning of the study, each resident is randomly assigned to either the intervention group (VL group) or the control group (DL group) in a 1:1 allocation. Each resident then performs all tracheal intubations within their assigned group. This approach ensures that the decision to randomize is made only at the outset of the study, with no switching between groups thereafter. This implies that each participant is immediately aware of their assigned study group following the enrolment phase and throughout the entirety of the study. The study employs Randomizer AT, a randomization software developed by the Medical University of Graz Institute for Medical Informatics, Statistics, and Documentation (IMI). Therefore, factors such as gender distribution cannot be influenced.

### Concealment mechanism {16b}

The randomization process and the data collected are treated in strict confidence and are known only to the principal investigator. Furthermore, all members of the study team are responsible for accurately recording the results. The pseudonymized study questionnaires are collected by the study director at regular intervals in person. Subsequently, the study personnel transfer these data items into a pseudonymized table. The decoding list for the pseudonyms is not accessible or known to the study personnel. This guarantees the anonymity of the study participants.

### Implementation {16c}

After obtaining consent from the residents, the project director will initiate automated randomization and allocate participants to either the control or intervention group. Randomization is not influenced by residents or other people in the department.

## Assignment of interventions: blinding

### Who will be blinded {17a}

The JuniorDoc-VL-Study is a patient-blinded study.

### Procedure for unblinding if needed {17b}

Not necessary, as there is no blinding.

## Data collection and management

### Plans for assessment and collection of outcomes {18a}

The time points for patient recruitment and intervention were recorded. Table 1 describes the data collection and processing methods, while Sect. 12 outlines the study instruments used to assess the outcomes. The collected data was entered into a (Microsoft Excel, Microsoft Deutschland GmbH, Version 2021) electronic data system.

### Plans to promote participant retention and complete follow-up {18b}

To promote participant retention and thorough documentation, the research team will conduct regular motivational discussions with the residents. Furthermore, the study team conducts periodic unannounced visits.

### Data management {19}

The study stages are documented in compliance with German and European data protection laws.

Patient identification data is only accessible to supervising doctors for routine care and is not recorded by this study, making patient re-identification impossible. The pseudonymized study data (data collection forms) will be stored in the archives of the University Surgical Clinic for ten years due to legal requirements. Third parties do not have access to the pseudonymization list. The list is safely stored and managed by the study directors in a locked office, without third access. Once the participating residents have carried out and recorded 200 ETIs, the data is anonymized in accordance with Sect. 13 Paragraph 2 LDSG BW/Germany.

### Confidentiality {27}

The sensitive data of all residents is archived, locked, and inaccessible to others. The data is immediately pseudonymized and anonymized as soon as the 200 intubations are completed. All anonymized original documents will be kept locked in the clinical research unit of the Department of Anesthesiology for the next ten years after publication. The study data will be handled in accordance with the German Federal Data Protection Act, which implements Directive 95/46/EC on data protection (Data Protection Directive). The electronic study database is anonymized and also stored for 10 years after publication.

### Plans for collection, laboratory evaluation, and storage of biological specimens for genetic or molecular analysis in this trial/future use {33}

There will be no biological specimens collected in the trial.

## Statistical methods

### Statistical methods for primary and secondary outcomes {20a}

A parallel two-group design will be used to test whether the Group 1 mean is different from the Group 2 mean (H0: μ1 − μ2 = 0 versus H1: μ1 − μ2 ≠ 0). The comparison will be made using a two-sided, two-sample equal-variance t-test, with a Type I error rate (α) of 0.05. The common standard deviation for both groups is assumed to be 10. The distribution of the data of the primary endpoint (FPS) is tested for normality using the Shapiro-Wilk test. In addition, graphical methods such as histograms and Q-Q plots are used to visually assess the distribution of the data. To compare FPS values between groups, either the parametric t-test (for normally distributed data) or the non-parametric Mann-Whitney U-test (for non-normally distributed data) is used, depending on the distribution. The choice of test was made based on the results of the normality test. Multiple logistic regression analysis of subgroup factors will allow us to assess the factors affecting FPS when comparing DL with VL, such as age, sex, ASA, BMI and provider experience. Cox regression can be used to evaluate the combined impact of the method and other explanatory variables. We used the following software for the calculation PASS 2024 Power Analysis and Sample Size Software (2024). NCSS, LLC. Kaysville, Utah, USA.

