### Criteria for discontinuing or modifying allocated interventions {11b}

Study participants may withdraw from the study at any time and without providing a reason, irrespective of their current stage in the study process. This includes scenarios such as the termination of their employment or relocation to another hospital. As a university hospital, we benefit from attracting staff with a strong interest in academic and scientific endeavors, which serves as a motivating factor for study participation. To ensure continuous support, a member of the study team is readily available to address any questions or concerns raised by participating residents. If, for whatever reason, the participants no longer wish to participate in the study, there will be no negative consequences. Likewise, no financial or other incentives will be given to participate in the study.

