### Sample size {14}

The calculation of the sample size was based on achieving successful tracheal intubation on the first attempt and on organizational aspects and realistic feasibility. In recent trials, the VL demonstrated a first-attempt success rate of 92–97% in a mixed resident population. The study’s power was determined by assuming an 80% first-pass success rate in the DL group [1] and 92–94% in the VL group [16, 18]. This study was chosen for the sample size calculation because the aim was to compare VL and DL in first-year anesthesia residents in the operating room. Based on the current first-pass success rate, we hypothesized that a 10% increase in the VL group compared to the DL group would constitute a significant improvement in advanced airway management. To detect a difference in means of 10, with sample sizes of 15 in Group 1 (VL) and 15 in Group 2 (DL), the power is 0.66262. The power was computed using PASS 2024, version 24.0.2 NCSS, LLC. Kaysville, UT, USA.

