### Methods in analysis to handle protocol non-adherence and any statistical methods to handle missing data {20c}

Only complete data will be evaluated in this study. As the study forms are completed by the residents themselves, we anticipate no issues. The analysis is based on the intention-to-treat principle.

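### The t-test branch of the primary analysis assumes equal variances that the plan's own rates make doubtful; Welch's test removes that dependence at almost no cost

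*Protocol article*

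**What the plan says.** Protocol article, section {20a}, compares the group means of FPS with a "two-sided, two-sample equal-variance t-test", "with a Type I error rate (α) of 0.05". It adds: "The common standard deviation for both groups is assumed to be 10". A Shapiro-Wilk test with plots decides between this test and a rank test: "the non-parametric Mann-Whitney U-test (for non-normally distributed data) is used, depending on the distribution".

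Section {14} plans 15 residents per arm. It assumes 80% FPS for DL and 92–94% for VL, takes a difference of 10 points as the target, and reports that "the power is 0.66262". The group sizes of 15 imply that the unit of analysis is the resident's FPS percentage, each based on 200 intubations.

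Two further statements bear on the final arm sizes. Section {11b}: "Study participants may withdraw from the study at any time". Section {20c}: "Only complete data will be evaluated in this study". The article gives no SD by arm, no dropout rate and no expected imbalance.

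**The concern.** A common SD of 10 fits poorly with a VL mean of 92–94% on a scale that ends at 100%. If VL residents cluster near the top, their spread should be smaller than that of DL residents.

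The pooled t-test tolerates unequal spread when the arms are equal in size, but less well when they are not. If the larger arm has the smaller SD, the pooled standard error is too small: intervals are too narrow and false positives rise. If the larger arm has the larger SD, the test is conservative. With about 15 residents per arm, two or three withdrawals on one side are enough to unbalance the arms. The validity of the main result would then depend on who happened to leave.

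**Working it through.** **1. The plan's own power figure.** Inputs: difference 10, SD 10, 15 per arm, two-sided α 0.05, equal-variance t-test. Noncentrality = 10 / (10 × √(2/15)) = 2.739 with 28 df, which gives power 0.753, not 0.66262. The printed value would match a difference of 9.00 with SD 10, or SD 11.11 with a difference of 10. This is a separate matter to reconcile between sections {14} and {20a}; the point here does not rest on it.

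**2. Does a common SD of 10 fit the expected means?** For a normal VL distribution with SD 10:
- mean 92: (100 − 92)/10 = 0.8 SD, so 21% of residents would lie above 100%
- mean 94: (100 − 94)/10 = 0.6 SD, so 27% would

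**3. What SD ratio is plausible?** The documents give none, so this is an assumption. Scaling spread by √(p(1 − p)) gives VL:DL ratios of √(0.0736/0.16) = 0.68 at 92% v 80%, and √(0.0564/0.16) = 0.59 at 94% v 80%. Ratios from 1 down to 0.33 were examined, with the DL SD held at 10.

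**4. Why arm size matters.** The true variance of the mean difference is σ₁²/n₁ + σ₂²/n₂. The pooled test estimates s_p²(1/n₁ + 1/n₂), with s_p² = [(n₁ − 1)s₁² + (n₂ − 1)s₂²]/(n₁ + n₂ − 2). Taking VL SD 6.8 and DL SD 10:
- 15:15: both equal 9.75, so there is no bias.
- 15 VL:12 DL: true 46.24/15 + 100/12 = 11.42; pooled (14 × 46.24 + 11 × 100)/25 × 0.15 = 10.48, about 8% too small.
- 12 VL:15 DL: true 46.24/12 + 100/15 = 10.52; pooled (11 × 46.24 + 14 × 100)/25 × 0.15 = 11.45, about 9% too large.

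**5. Simulated type I error of the pooled test** (normal data, equal means, nominal 5%):

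| VL:DL residents | SD ratio 1 | 0.7 | 0.5 | 0.33 |
|---|---|---|---|---|
| 15:15 | 4.9% | 5.0% | 5.4% | 5.6% |
| 15:13 | 4.9% | 5.7% | 6.5% | 7.1% |
| 15:12 | 5.0% | 6.0% | 7.0% | 8.2% |
| 12:15 | 5.1% | 4.3% | 3.9% | 3.7% |
| 18:12 | 5.0% | 6.9% | 8.6% | 10.3% |
| 20:10 | 4.9% | 8.2% | 11.4% | 14.7% |

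At ratios of 0.59–0.68 and 15 VL:12 DL the figure is 6.2–6.5%. Welch's test gave 4.8–5.1% in every normal-data setting.

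**6. Interval coverage at the expected means** (93% v 80%, DL SD 10, VL SD 3–5, nominal 95%). Pooled coverage:
- 15:15: 94.0–94.7%
- 15 VL:13 DL: 92.3–93.3%
- 15 VL:12 DL: 91.0–92.8%
- 18 VL:12 DL: 88.9–91.2%
- 12 VL:18 DL: 96.8–97.2%

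With VL SD 6.8, pooled coverage at 15 VL:12 DL is about 94%. Welch intervals covered about 94–95% throughout.

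**7. Bounded, skewed data** (beta-binomial rates out of 200, common mean 90%, SD 5 v 10). At 15:15 the pooled test rejects in 6.6% and Welch in 6.4%; at 15 VL:12 DL, 8.1% and 6.9%. Welch is closer to nominal but not exact, because skewness adds its own error.

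**8. Cost in power.** At 15:15 with SD about 10 in both arms (beta-binomial, 90% v 80%), power is 72.3% pooled and 72.1% Welch.

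**The case against.** A reader might infer that the VL ceiling pushes the type I error well away from 5%. The documents do not support that. Type I error is defined under equal means, where the ceiling acts on both arms alike; unequal spread would then have to come from different between-resident variation, for which no figure is given. The 92–94% v 80% contrast is the alternative hypothesis, so the ceiling bears on the confidence interval at the expected means, not on the null.

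The larger error rates also rest on splits that the plan does not predict. At the planned 15:15 the pooled test is adequate. Splits such as 18:12 keep all 30 residents, so they would come from randomisation, not withdrawal. Blocking may well be set out in the full protocol, and its absence from an article is no finding. Even under simple randomisation of 30, with SD 5 v 10, the average type I error is only 5.7%. Section {20c} does not say whether complete data refers to forms or to residents, and it also claims intention-to-treat, so the exclusion of residents who leave is an inference. All of this stands and limits the size of the point.

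It is also fair that markedly skewed data may be sent to the Mann-Whitney test. That does not remove the t-test branch. In simulated trials with DL 80% (SD 10) and VL 93% (SD 3–5), both arms passed Shapiro-Wilk in 58–77% of runs, so the pooled test would often be the one used.

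**Conclusion.** The concern holds in a modest form. The equal-variance assumption sits badly with the plan's own expected rates, and the pooled test is protected only while the arms stay close to equal in size. After a loss of three residents from one arm, with assumed SD ratios of about 0.6–0.7, type I error is about 6–7% if DL is the smaller arm and about 4% if VL is. Coverage of the pooled 95% interval at the expected means falls to about 91–94% at 15 VL:12 DL for assumed VL SDs of 3–6.8.

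Error rates of 8–11% need more extreme conditions: for example an SD ratio of 0.5 with 18:12 (8.6%) or 20:10 (11.4%), or a ratio near one third with 15:12 (8.2%). The SD ratios and the unequal splits are assumptions, not figures from the documents. This is a worthwhile robustness gain at the level of a suggestion.

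**What to change.** In the t-test branch of section {20a}, replace the equal-variance t-test with the two-sided Welch (unequal-variance) t-test at α 0.05, and state that the difference in mean resident-level FPS will be reported with its Welch 95% confidence interval. The common SD of 10 can remain as a planning assumption for the power calculation, labelled as such.

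The cost is a small wording change through the amendment route in section {25}; recruitment is expected to run to the end of 2027. The power loss is negligible if the variances are equal. With 15 VL:12 DL and a VL SD of about 5, the pooled test appears more powerful (88.6% v 84.5% at 90% v 80%), but that advantage goes with its inflated type I error. With 12 VL:15 DL, Welch is the more powerful (89.0% v 87.0%). Welch does not cure skewness near the ceiling, so the text should not present it as exact there.

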### Intervention description {11a}

After providing informed consent, residents are given an evaluation form to independently document endotracheal intubation (ETI) procedures they have previously performed during their internship or medical school training. This process enables us to assess the extent of each resident's prior experience with advanced airway management. In this study, the intervention group will utilize video laryngoscopy as the standard method for airway management, specifically employing the hyperangulated D-Blade® (C-MAC®, Karl Storz, Germany) for all elective intubations [6, 8]. To ensure the inclusion of a patient population representative of real-world clinical scenarios (real-world data), the study incorporates both patients with no anticipated risk of difficult tracheal intubation and those with an expected difficult airway.

All patients are monitored for electrocardiography (ECG), oxygen saturation (SpO_2_), and arterial blood pressure (non-invasively or invasively, as appropriate). In the VL group, a malleable style was utilized for tracheal tube placement. This approach is consistent with the clinical standard. Preoxygenation is achieved using the device selected by the provider based on patient characteristics and the clinical standard operating procedure (EtO2 > 80%).

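### The primary test of first-pass success is chosen by a normality test on the trial data, so the stated hypothesis on means is not the one tested after a switch

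*Protocol article*

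**What the plan says.** All of this stands in one paragraph of the protocol article, Statistical methods for primary and secondary outcomes {20a}.

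- The hypothesis concerns means: "H0: μ1 − μ2 = 0 versus H1: μ1 − μ2 ≠ 0".
- One test is fixed for it: "The comparison will be made using a two-sided, two-sample equal-variance t-test", "with a Type I error rate (α) of 0.05".
- The spread is a planning assumption: "The common standard deviation for both groups is assumed to be 10".
- The first-pass success (FPS) data are then checked with Shapiro-Wilk, histograms and Q-Q plots. The groups are compared by t-test if the data look normal and by Mann-Whitney U if they do not: "The choice of test was made based on the results of the normality test".

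The article gives no significance level for the pre-test and does not say whether it is run per arm or on all 30 residents together.

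Sample size {14} sets 15 residents per arm, 80% FPS for DL and 92-94% for VL, and a target difference ("To detect a difference in means of 10"). Each resident contributes 200 intubations.

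On prior experience, Intervention description {11a} has residents "independently document endotracheal intubation (ETI) procedures they have previously performed during their internship or medical school training". Neither candidate primary test uses that count. Provider experience does appear in the additional multiple logistic regression in {20a}, and experience in direct and indirect laryngoscopy is listed under Subgroups.

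**The concern.** The paragraph contradicts itself: it fixes a t-test and then makes the t-test conditional. The two tests also answer different questions. The t-test concerns the difference in mean FPS. Mann-Whitney concerns whether residents in one arm tend to rank above those in the other, and it can reject when the means are equal but the shapes or spreads differ. After a switch, the p-value no longer refers to the stated null, and a difference in means with its CI no longer belongs to the test reported.

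This would matter little if a switch were rare. But FPS is a percentage with a ceiling, and the plan expects VL residents close to it. At stake is the interpretation of the primary result and, if the arms differ in spread, its type I error for the null as written.

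**Working it through.** **Inputs.** From Sample size {14}: 15 per arm, difference 10, DL 80%, VL 92-94%. From {20a}: SD 10, two-sided alpha 0.05. From Participant timeline {13}: 200 intubations per resident. Differences and SDs are read as percentage points of resident-level FPS.

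**The plan's own power.** For the "two-sided, two-sample equal-variance t-test", the noncentrality is (10/10) × √(15/2) = 2.739 with 28 df, which gives power 0.753. The article states 0.66262. That value corresponds to a standardised difference of 0.90 (9 with SD 10, or 10 with SD 11.1). This is a separate matter. For the present point, both figures describe the t-test.

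**Is normality tenable?** A normal distribution with mean 93 and SD 10 puts P(Z > (100 − 93)/10) = P(Z > 0.7) = 0.242 of VL residents above 100%. With an SD of 10 that close to the ceiling, the distribution must be skewed.

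**Simulation model (assumption).** Each resident's true rate is beta-distributed with mean m and SD s: k = m(1 − m)/s² − 1, with parameters mk and (1 − m)k. For m = 0.90 and s = 0.10, k = 0.09/0.01 − 1 = 8, so the parameters are 7.2 and 0.8. Observed FPS is binomial with 200 intubations. The rule switches to Mann-Whitney if Shapiro-Wilk gives p < 0.05 in either arm, unless pooled testing is named. Settings used 4,000 to 10,000 trials each.

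**How often the test switches**

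| DL v VL | SDs | Switch |
|---|---|---|
| 80 v 90% | 10, 10 | about 73% (59% if pooled) |
| 80 v 92% | 10, 10 | about 90% |
| 80 v 93% | 10, 10 | about 96% |
| 80 v 92% | DL 10, VL 5 | about 39% |
| 80 v 92% | 5 and 4 | about 24% |

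With truly normal data the rate is 9%. In the three SD 10 rows, the t-test and Mann-Whitney disagree on significance in about 8-11% of trials.

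**Type I error for the null on means**

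| Setting | Two-stage rule | Fixed test |
|---|---|---|
| Both arms the same distribution | 0.045-0.056 | about 0.05 |
| Means 85%, SDs 10 and 5 | 0.078 (pooled 0.063) | 0.054 (t-test) |
| Means 85%, SDs 12 and 5 | 0.11 (pooled 0.088) | 0.057 (Welch) |

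**Power, two-stage rule v Welch, SD 10:** 0.81 v about 0.72 (80 v 90%), 0.93 v 0.85 (80 v 92%), 0.96 v 0.88 (80 v 93%).

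**Adjusting for prior intubations.** The documents give no correlation r with FPS, so r is an assumption. At a difference of 10 and SD 10, simulated ordinary ANCOVA has power 0.733 at r = 0, 0.779 at r = 0.3 and 0.849 at r = 0.5, against about 0.75 unadjusted. The gain starts at roughly r = 0.2. With HC3 standard errors, power is about 0.69-0.70 at R² = 0 and 0.74 at R² = 0.1.

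**The case against.** The strongest defence is that the two-stage rule does little harm and some good. When both arms share a distribution, type I error is held near 5%. With skewed rates at SD 10 the rule has more power than a fixed Welch test, so much of the 8-11% disagreement is Mann-Whitney detecting a real difference. The plan assumes a common SD, and the inflation needs unequal spreads with equal means. The switch rates also depend on SD 10 holding near the ceiling. All of this stands, and it limits the size of the point.

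It does not remove the contradiction. The article names one hypothesis and one test, then hands the choice to the data. Unequal spread is also plausible, because the spread of a percentage tends to shrink near 100%, where VL is expected.

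A reader might go further and infer that the plan ignores prior intubation experience and so gives up precision. The documents do not support that. Experience is absent only from the primary test and is named for the additional regression. An unadjusted comparison in a randomised trial is valid. All participants are new residents, so earlier experience may vary little, and at low correlation adjustment gains nothing with 30 residents.

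**Conclusion.** The point holds as a fault in how the primary analysis is fixed. The stated null is on means, but the test that delivers the primary p-value is selected on the same data and may not address that null. On the plan's own SD of 10, with beta-distributed resident rates, a switch is the likely outcome (about 73-96%). With a VL SD of 5 it is a minority outcome (39%) under per-arm pre-testing.

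A reader might infer that the rule inflates type I error in general. It does not. The rise to about 8% or 11% depends on equal means with SDs of 10 and 5 or 12 and 5, and is smaller with pooled pre-testing. Nor can it be said without condition that the stated power belongs to a test that will seldom be used, since that depends on the spread in the VL arm. Any precision gain from adjusting for prior intubations remains an assumption.

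**What to change.** In {20a}, delete the Shapiro-Wilk switch and name one estimand and one test that match the stated null: the difference in mean resident-level FPS between arms, tested with a two-sided Welch (unequal-variance) test at 0.05 and reported with a 95% CI. Keep Mann-Whitney as a prespecified sensitivity analysis, and use histograms and Q-Q plots for description only. Restate the power in {14} for the test chosen.

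Adjustment for the recorded number of prior intubations can be a prespecified supportive analysis. It should not be presented as a sure gain in precision.

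The change is an amendment to the text. Recruitment is expected to run to 31 December 2027, so it can be made before the analysis. It does have a cost: if FPS is strongly skewed at SD 10, Welch has less power than the two-stage rule (about 0.72 v 0.81 at 80 v 90%). If the sponsor would rather keep the rank test's power, the alternative is to prespecify Mann-Whitney alone and reword the hypothesis to match. Either choice must be fixed before the data are seen.
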